All these previous studies were performed using 300 to 600 mg of intravenous iron sucrose administered in a period ranging from 2 to 6 days. Ferric carboxymaltose (FC) has considerable advantages over iron sucrose because it allows doses of 1 g in a single session, equivalent to 1000 mg of iron sucrose. Moreover, FC also provides an excellent tolerability and safety profile [17-19]. Therefore, it is very useful in situations where quick replacement is required as is the case of HF. It has been used successfully in iron deficiency-, inflammatory-, and in postpartum anemia, however there are no data on its efficacy in HF.

Preliminary results of perioperative use of EPO in HF are promising; however, these results suffer from bias because trials were not randomized and/or blinded. On the other hand, all studies were performed with iron sucrose, so that any additional benefit related to FC cannot be extrapolated. Therefore we have promoted and developed a phase III clinical trial (CT) in order to definitively assess the benefit of RCP saving with the use of EPO with/without FC in patients with HF. The main objective of the present CT was to evaluate the efficacy of combined treatment of i.v. ferric carboxymaltose and erythropoietin (EPOFE arm) versus i.v. ferric carboxymaltose (FE arm) versus placebo (placebo arm) in reducing the percentage of patients who receive blood transfusions in the perioperative period of hip fracture intervention.

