### Sample size calculation

Sample size was calculated as follows:

-To obtain statistical significance in the comparison between the i.v. iron + EPO arm compared to placebo. The treatment arm exclusively with iron is only used in the evaluation of results, but not in the sample size calculation.

-To obtain a confidence level of 95% and 80% power.

-To be single sided.

-To obtain a reduction in the primary endpoint of 20% (percentage of patients who need transfusions), which is considered as clinically significant in the literature. According to this, we would expect the percentage of patients who need to be transfused in the placebo group to be 60% and in the treatment group 40%.

-Sample size was calculated online using SISA http://www.quantitativeskills.com/sisa/calculations/samsize.htm. A total of 87 patients per arm are needed with the foregoing conditions.

-Taking into account a percentage of drop-outs of 15% per arm, the total number of patients per arm is set at 87 × (1/1-0.15) = 102, a total of 306 patients.

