### Statistical analysis

Both intention to treat (ITT) and per protocol analysis will be performed. The ITT analysis will include all patients who agreed to participate in the study, signed the informed consent, and had been randomized. Per protocol analysis will include the patients who were randomized, received the dose of erythropoietin and ferric carboxymaltose (EPOFE arm), ferric carboxymaltose (FE arm), or placebo (PLACEBO arm), and were operated on; excluding those who discontinued the trial, or received a red-cell pack in a different format than specified in the protocol. Violation of the blinded assignment will be also excluded in the per protocol analysis.

A chi-square test will be performed in order to establish the comparative analysis of the primary efficacy outcome, secondary efficacy, safety and cost endpoints between different arms of the study (Yates correction and, where necessary, Fisher exact test) for qualitative endpoints. Analysis of variance (with post-hoc test of Tukey and T3-Dunette)/Kruskal-Wallis test will be performed for quantitative variables. Differences between groups will be quantified using 95% confidence intervals.

The cost-effectiveness analysis will be performed by incremental cost-effectiveness method, using each patient who did not require RCP transfusion as the primary efficacy unit; each patient surviving at discharge and 60 days after discharge as the high efficiency unit; and the sum of all previously recorded costs of hospitalization as the cost unit. The calculations will be performed as follows: incremental cost-effectiveness (Euros per unit of efficiency gains) = NNT × (cost per a) option patient - cost per b) option patient).

All calculations will be performed using SPSS 18.0. The threshold of statistical significance is set at *p *< 0.05.

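### The sample size rests on EPOFE versus placebo alone, but the primary endpoint is tested across three arms at one p < 0.05 with no confirmatory contrast, order or adjustment

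*Protocol article*

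**What the plan says.** The Sample size calculation section states its aim: "To obtain statistical significance in the comparison between the i.v. iron + EPO arm compared to placebo". It adds: "The treatment arm exclusively with iron is only used in the evaluation of results, but not in the sample size calculation". The design values are "To obtain a confidence level of 95% and 80% power", a one-sided test, and transfusion in 60% of placebo patients against 40% of treated patients. This gives 87 patients per arm, raised to 102 for drop-out, 306 in total.

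The main objective at the end of the Background section is a three-way comparison of EPOFE, FE and placebo on the percentage transfused. No pair is ranked first.

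The Statistical analysis section prescribes chi-square, with Yates correction and Fisher's exact test where needed, for the "comparative analysis of the primary efficacy outcome, secondary efficacy, safety and cost endpoints between different arms of the study". For quantitative variables it adds "Analysis of variance (with post-hoc test of Tukey and T3-Dunette", with Kruskal-Wallis as the alternative. One significance threshold, p < 0.05, covers everything, and 95% confidence intervals are planned for group differences.

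**The concern.** The sizing section gives the trial one main question. The objective and the analysis section treat the three arms symmetrically. As the analysis rule is worded, a significant result on the primary endpoint from any pair of arms could be presented as the trial's positive finding, although only one pair was sized.

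The article is not silent on multiplicity between arms. It provides post-hoc procedures for means but none for the binary primary endpoint, where control matters most.

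Two things are at stake. One is the chance of a false positive primary claim. The other is the weight given to the FE contrasts, for which no power was planned. If FE lay midway at 50% (an assumption; the article gives no FE rate), FE versus placebo would have 28% power at 87 per arm and 32% at 102. A non-significant FE result would then say little about whether iron alone works.

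**Working it through.** **Inputs.** From Sample size calculation: rates 60% and 40%, one-sided 0.05, 80% power, 87 evaluable and 102 randomised per arm. From Statistical analysis: chi-square with Yates or Fisher, p < 0.05. Assumed: two-sided testing in the analysis (the section gives no side) and an FE rate between 40% and 60%.

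**1. The plan's own figure.** Without continuity correction:

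n = [1.645 × √(2 × 0.5 × 0.5) + 0.842 × √(0.24 + 0.24)]² / 0.20² = (1.163 + 0.583)² / 0.04 = 76.2, so 77.

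With continuity correction:

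n = (76.2 / 4) × [1 + √(1 + 4 / (76.2 × 0.20))]² = 85.9, so 86.

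The stated 87 agrees to within one patient. Drop-out: 87 / 0.85 = 102.4, stated as 102; 3 × 102 = 306. The figure therefore belongs to a single two-arm comparison, and its arithmetic is not at issue here.

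**2. Pairwise reading, nominal error.** Three pairwise z-tests on equal arms share data, so the familywise error is the tail of the studentized range for three groups:

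P(range > 1.96 × √2 = 2.772) = 12.2%.

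Treating the tests as independent would give 1 − 0.95³ = 14.3%, which is too high. For the two comparisons with placebo only (correlation 0.5), the figure is 9.1%.

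**3. Pairwise reading, the tests as named.** Simulation under the global null: 1,000,000 runs per setting, common rates of 40%, 50% and 60%, 87 and 102 per arm.

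| Tests, two-sided 0.05 | Uncorrected | With Yates |
|---|---|---|
| One pair | 5.3 to 5.8% | 3.7 to 4.2% |
| Three pairs | 12.9 to 14.1% | 9.2 to 10.4% |
| Two pairs, each against placebo | 9.6 to 10.6% | 6.7 to 7.7% |

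Yates makes each test conservative, so the realised familywise rate falls below the nominal 12% but stays above 5%.

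**4. Single 3x2 reading.** The same simulation gives 4.9 to 5.1% for one omnibus chi-square, and the same when pairs are tested only after a significant omnibus result. Power follows from the noncentral chi-square with 2 df and

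λ = n × Σ(pᵢ − p̄)² / [p̄(1 − p̄)].

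- FE at 50%: λ = 87 × 0.0200 / 0.2500 = 6.96, power 65%.
- FE at 40% or 60%: λ = 87 × 0.02667 / 0.2489 = 9.32, power 79%.
- With all 102 per arm evaluable, the same two cases give 73% and 85%.

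At the 87 evaluable patients on which the plan rests, the omnibus test stays below 80% over the whole assumed range.

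**The case against.** The strongest objection is that the text never prescribes three pairwise tests. It speaks of a chi-square test between arms and one threshold. Read as a single 3x2 test, or as a 3x2 test that gates the pairs, the error is about 5%. With exactly three arms, such gating is a closed procedure and controls the familywise error. This stands: a reader might infer that the plan has a 12% error rate, and the article does not support that without the condition of ungated pairwise testing. Against it, Yates correction belongs to 2x2 tables, which points to pairs, and no gate is stated. The 3x2 reading also brings its own mismatch with the sample size.

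Second, the sizing section shows which comparison carries the design, so it would go too far to say that the intended main contrast cannot be identified. This also stands. But that section says only what was sized; neither the objective nor the analysis section makes that contrast the confirmatory one.

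Third, the familywise figures count false harm as well as false benefit. At two-sided 0.05, false claims of benefit against placebo total 3.3 to 3.9% with Yates and 4.8 to 5.3% without. If the one-sided 0.05 of the sizing section also governs the analysis, they rise to 6.6 to 7.2% with Yates and 8.8 to 9.7% without. The size of the problem therefore depends on a sidedness that the analysis section does not state.

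Fourth, part of the omnibus shortfall comes from sidedness: a two-sided test of the sized pair alone, without continuity correction, has about 76% power at 87 per arm.

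Last, a testing order is often left to a statistical analysis plan. Here, however, the article itself states the test, the corrections, the post-hoc methods and the threshold, and that stated rule does not match the contrast it sized.

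**Conclusion.** The point holds, with a size that depends on the reading. Under ungated pairwise testing at two-sided 0.05, the familywise error under the global null is about 12% nominally and about 9 to 10% with the protocol's Yates correction; for the two comparisons with placebo it is about 7 to 8% with Yates. Under a single 3x2 test the error is about 5%, but power at 87 per arm is 65 to 79% if FE lies between 40% and 60%. That FE range is an assumption.

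A reader might conclude that an omnibus gate is invalid. It is not: the case against it here is power, not error control. All figures concern multiplicity between arms only; the interim look at the primary endpoint and the sidedness of the analysis are separate matters. Neither reading fits the sample size as it stands, so the analysis section should be amended.

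**What to change.** In Statistical analysis, name EPOFE versus placebo as the single confirmatory test of the primary endpoint at full alpha. Then test FE versus placebo, and after it EPOFE versus FE, each only if the preceding test is significant. Otherwise report these two contrasts as estimates with the 95% confidence intervals already planned.

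This holds the error from multiple arm comparisons at the nominal 5%, with no extra patients and no loss of power for the sized contrast. The cost is that the FE contrasts lose any confirmatory claim if the first test fails. By comparison, Bonferroni over all three pairs (two-sided 0.05 / 3, no continuity correction) would need about 130 evaluable and 153 randomised patients per arm for the 60% versus 40% difference; at 87 per arm its power would be about 60%.

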**Methods/Design:**

Multicentric, phase III, randomized, controlled, double blinded, parallel groups clinical trial. Patients > 65 years admitted to hospital with a hip fracture will be eligible to participate. Patients will be treated with either a single dosage of i.v. ferric carboxymaltose of 1 g and subcutaneous erythropoietin (40.000 IU), or i.v. ferric carboxymaltose and subcutaneous placebo, or i.v. placebo and subcutaneous placebo. Follow-up will be performed until 60 days after discharge, assessing transfusion needs, morbidity, mortality, safety, costs, and health-related quality of life. Intention to treat, as well as per protocol, and incremental cost-effectiveness analysis will be performed. The number of recruited patients per arm is set at 102, a total of 306 patients.

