### Outcome measures

The primary outcome measure will be the percentage of patients who receive red-cell transfusion during hospitalization, and after 60 days of hospital discharge.

Secondary outcome measures will be the following related with efficacy, safety, HRQoL, and cost-effectiveness

Efficacy end-points: the average number of red-cell packs needed per patient at the end of the study, the average number of red-cell packs needed per patient (only transfused patients), the average hemoglobin level at 24 and 72 hours postoperative period and at hospital discharge, and the total number of hospitalization days.

Safety endpoints: the death rate from all causes at the end of the study; and adverse events including the following clinical complications: vascular events, all kinds of cerebrovascular accidents, acute coronary syndrome, thrombosis, arterial embolism, heart failure, acute/chronic exacerbation of respiratory failure, delirium, thromboembolic disease, catheter-related phlebitis; renal failure; infectious complications: pneumonia, urinary tract infection, surgical-site infection; and all side effects detailed on the EPO and FC data sheet.

HRQoL end-point: Quality of life will be assessed by the Short form 36 version 2 (SF-36) for acute patients [20]. This questionnaire will be administered at inclusion and 60 days after hospital discharge.

Cost-effectiveness end-point: An analysis of incremental cost-effectiveness (using as a primary endpoint each patient not requiring a transfusion, and as a secondary endpoint every patient who survived the index admission) will be performed.

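### The cost-effectiveness analysis sets costs of hospitalization, with no stated end date, against effects that run to 60 days after discharge, and two sections define the survival unit differently

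*Protocol article*

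**What the plan says.** Four places in the protocol article bear on this.

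- **Statistical analysis, cost unit:** "the sum of all previously recorded costs of hospitalization as the cost unit". No closing date is given. The phrase does not say whether readmissions count, and the article does not describe the cost recording it refers back to.
- **Statistical analysis, effect units:** the first is defined by "using each patient who did not require RCP transfusion as the primary efficacy unit", with no time window in that sentence. The second is "each patient surviving at discharge and 60 days after discharge as the high efficiency unit". The ratio is computed as "NNT × (cost per a) option patient - cost per b) option patient".
- **Outcome measures:** the cost-effectiveness end-point takes "as a secondary endpoint every patient who survived the index admission". The same section defines the trial's transfusion outcome as "the percentage of patients who receive red-cell transfusion during hospitalization, and after 60 days of hospital discharge".
- **Abstract, Methods/Design:** "Follow-up will be performed until 60 days after discharge, assessing transfusion needs, morbidity, mortality, safety, costs, and health-related quality of life". Costs are therefore listed among the items followed after discharge.

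**The concern.** An incremental cost-effectiveness ratio compares a cost difference with an effect difference over one period. If the effect is counted to 60 days after discharge and the cost stops at the hospital stay, a late transfusion, complication or death changes the effect while the cost of the associated care may be left out.

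The safety outcomes include thrombosis, infection and heart failure. These can occur and be paid for after discharge, and they could differ between arms. The Abstract names cost-effectiveness beside safety and efficacy in the objective, so the ratio is likely to be reported and read.

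The survival unit raises a separate difficulty. Deaths between discharge and day 60 count under the Statistical analysis section and do not count under Outcome measures. Two analysts, each following one section, could report different survival ratios from the same data.

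**Working it through.** The article states no cost, NNT or cost-effectiveness ratio, so there is no figure of the plan's own to reproduce. The check has three steps.

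**1. Is the formula valid?** With effect difference ΔE (as a proportion) and per-patient cost difference ΔC, NNT = 1/ΔE. Then NNT × ΔC = ΔC/ΔE, which is the usual incremental ratio. The formula is sound, and only the periods covered by ΔC and ΔE are in question.

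**2. Which pairs of cost and effect match?** Here costs of hospitalization are read as the index stay.

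| Effect | Where defined | Effect period | Matches index-stay costs? |
|---|---|---|---|
| Survival of the index admission | Outcome measures | to discharge | yes |
| Survival at discharge | Statistical analysis | to discharge | yes |
| Survival at 60 days after discharge | Statistical analysis | to day 60 | no |
| No transfusion | Statistical analysis | not stated | yes if in-hospital; no if the primary-outcome window applies |

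If the survival wording in Statistical analysis is meant as one composite (alive at both time points), it reduces to being alive at day 60. That section then contains no matched survival ratio.

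If costs of hospitalization also take in readmissions up to day 60, the gap narrows to care given without admission, such as an outpatient transfusion or treatment of a complication outside hospital. It does not close.

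**3. How much does an uncounted cost move the ratio?** Split the cost difference into a counted part ΔC(h) and an uncounted post-discharge part ΔC(p).

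- Ratio as worded: NNT × ΔC(h)
- Ratio with costs to day 60: NNT × [ΔC(h) + ΔC(p)]
- Shift: NNT × ΔC(p)

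The planning rates in Sample size calculation are 60% transfused on placebo and 40% on treatment. So ΔE = 0.60 − 0.40 = 0.20 and NNT = 1/0.20 = 5. Each euro of ΔC(p) moves the transfusion ratio by 5 euros per transfusion-free patient. Because the article gives no costs, the range below is an assumption:

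| Assumed ΔC(p), euros per patient | Shift in ratio, euros per transfusion-free patient |
|---|---|
| −200 | 5 × (−200) = −1,000 |
| −100 | 5 × (−100) = −500 |
| 0 | 0 |
| +100 | 5 × 100 = +500 |
| +200 | 5 × 200 = +1,000 |

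The shift can go either way, and it is zero if post-discharge costs do not differ between arms. For 60-day survival the multiplier is 1 divided by the survival difference. The article gives no such difference, so no figure is offered.

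**The case against.** The best defence is that the article condenses a fuller protocol and that its wording can be read consistently. The cost phrase refers to all costs previously recorded and has no end date. It does not say index admission, although Outcome measures uses that term when it means it. Readmission costs are hospitalization costs too. Since the Abstract says costs are assessed to 60 days, the phrase could include costs recorded in follow-up. Survival at discharge is matched in any case. The transfusion unit carries no window in the cost-effectiveness sentences, so giving it the primary-outcome window is an inference. On survival, Statistical analysis can be read as keeping the unit in Outcome measures and adding a second time point. Finally, the Discussion promises cost-effectiveness only if possible.

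Most of this stands, and it rules out three stronger readings that a reader might infer:

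- **That the ratio is wrong as defined.** The formula is correct, and a narrower cost scope gives a partial ratio. That ratio is biased only if the uncounted costs differ between arms.
- **That every effect runs past the costs, or that readmissions are certainly left out.** The article establishes neither.
- **That the 4–8% in the Background gives a survival difference from which to size the effect.** It is a range for the level of death during hospitalization, not a difference between arms, and it concerns the period in which costs and survival do match.

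The defence does not remove the core. Statistical analysis explicitly sets a cost unit described as hospitalization against survival at 60 days. Even the generous reading leaves out care given without admission. The two sections do state the survival unit differently, and an unseen analysis plan does not reconcile wording already fixed here.

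**Conclusion.** The point holds in limited form. As worded, the cost unit covers a period that is shorter than the 60-day survival effect it is set against, or undefined. The same applies to the transfusion effect if that takes the primary-outcome window. The cost wording sits badly with the Abstract's assessment of costs to 60 days, and Outcome measures and Statistical analysis give different survival units.

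The size is conditional. At the planning rates, the transfusion ratio moves by 5 euros for each uncounted euro of between-arm cost difference per patient. This assumes that the planned 20-point difference is observed, that transfusion is counted to day 60, and that some post-discharge cost is in fact left out. Whether the arms would differ in such costs cannot be judged from the article.

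This is a secondary economic analysis. The primary efficacy test and the sample size do not depend on it. The wording should be corrected because the correction is cheap and removes a real ambiguity.

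**What to change.** In Statistical analysis, state one cost period for each ratio and pair it with an effect over the same period:

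1. **Index admission:** untransfused at discharge, and alive at discharge, against index-admission costs.
2. **To Visit 4 (60 days after discharge):** untransfused to Visit 4, and alive at Visit 4, against index-admission costs plus the costs of readmission, post-discharge transfusion and treatment of post-discharge events.

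If post-discharge costs are not being recorded, restrict the ratios to the index admission and say so. Say whether the survival wording means two separate units or one composite, and give the same unit or units in Outcome measures and Statistical analysis.

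The cost is a few sentences of wording. If the 60-day ratios are kept, there is a little extra costing work as well. According to the Abstract, follow-up already assesses transfusion needs, morbidity, mortality and costs over that period, so no new visit is needed. Restricting the ratios to the index admission adds no work.

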### Interim analysis and stopping rules

An interim analysis will be performed when half of the patients are recruited, blinded to investigators in order to a) detect possible imbalances between the three arms of the trial with respect to a list of independent secondary endpoints, and b) assess whether the primary efficacy endpoint was obtained at this point in the trial. The list of independent secondary endpoints will include the following: age, sex, type of fracture (subcapital/intertrochanteric), baseline hemoglobin level and type of surgery.

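### The interim look at the primary endpoint has no boundary and no stated consequence; if the only threshold given, p<0.05, is used at both looks and success can be declared at either, the type I error for EPOFE vs placebo rises from 5% to about 8%

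*Protocol article*

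**What the plan says.** The protocol article, section Interim analysis and stopping rules, states: "An interim analysis will be performed when half of the patients are recruited". The analysis is blinded to investigators and has two purposes. One is to look for imbalance between the arms. The other is to "assess whether the primary efficacy endpoint was obtained at this point in the trial". Despite its heading, the section gives no boundary, no division of alpha between the looks, and no action that depends on the result.

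The section Statistical analysis specifies a chi-square test for the primary outcome, with Yates correction and, where needed, Fisher's exact test. It closes with one threshold: "The threshold of statistical significance is set at" p<0.05. That sentence is not confined to the final analysis.

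The section Sample size calculation rests on one comparison, EPOFE vs placebo, under the conditions "To obtain a confidence level of 95% and 80% power" and "To be single sided". It makes no allowance for a second look.

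The section Outcome measures defines the primary outcome over the hospital stay and the 60 days after discharge.

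**The concern.** Judging whether the primary endpoint has been met halfway through requires a comparison by arm, which makes it an efficacy look. Efficacy is then assessed twice, while the article offers one threshold and no rule linking the looks. An investigator or data analyst following the article has only p<0.05 to use each time. If a positive interim can end the trial or support a claim, a false positive has two chances to occur and the nominal 5% is exceeded.

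The gap would probably matter in practice. Under the planning assumptions a nominally significant interim is a realistic outcome (see the working), so someone would have to decide what to do with it. A boundary chosen after the interim result is known cannot restore control of the error rate.

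Timing adds a second weakness. Half recruitment is not half of the outcome information when the outcome window closes 60 days after discharge.

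**Working it through.** **Inputs from the protocol article.** Placebo 60%, treatment 40%, alpha 0.05 one-sided, power 80%, 87 per arm, 15% drop-out, 102 per arm, 306 in total (Sample size calculation). One interim at half recruitment, that is 306/2 = 153 patients or 51 per arm (Interim analysis and stopping rules). Threshold p<0.05; chi-square with Yates correction (Statistical analysis).

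**The plan's own figure.** With pooled variance under the null, one-sided:

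n = [1.645·√(2·0.5·0.5) + 0.842·√(0.24+0.24)]² / 0.20² = (1.163 + 0.583)² / 0.04 ≈ 76.2, rounded up to 77.

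With continuity correction:

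(76.2/4)·[1 + √(1 + 4/(76.2·0.20))]² ≈ 85.9, rounded up to 86.

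The plan states "A total of 87 patients per arm are needed with the foregoing conditions", which this reproduces to within one patient. Drop-out: 87/0.85 = 102.4, stated as 102; 3 × 102 = 306. The figure belongs to a single one-sided test with no interim.

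**Type I error of two unadjusted looks.** At information fraction 0.5 the two test statistics have correlation √0.5 = 0.707. The probability of crossing at either look is P(cross at 1) + P(cross at 2) − P(cross at both).

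- Two-sided 0.05 (limit 1.96): 0.05 + 0.05 − 0.0169 = 0.0831.
- One-sided 0.05 (limit 1.645): 0.05 + 0.05 − 0.0199 = 0.0801.
- Information fraction 0.4 to 0.6: 8.6% to 8.0% two-sided, 8.3% to 7.7% one-sided.

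The result therefore does not depend on whether the threshold is read as one-sided or two-sided.

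**The same with the stated test.** Simulated two-group comparison, 51 then 102 per arm, common rate 60%, two-sided 0.05:

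| Test | Final look only | Either look |
|---|---|---|
| Chi-square, uncorrected | 5.3% | 8.9% |
| Chi-square, Yates | 3.8% | 6.0% |

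With Yates at a common rate of 50% the figures are 4.2% and 6.7%. The relative rise with Yates is about 1.6-fold (6.0/3.8), close to that of the normal approximation (8.3/5.0 = 1.7).

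**How often the interim would cross.** With true rates of 60% and 40% and all 51 per arm evaluable, p<0.05 is reached in 56% of trials uncorrected and 48% with Yates. With about 43 evaluable per arm (51 × 0.85), the figures are 45% and 36%.

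**Boundaries that repair it** (two-sided, information fraction 0.5):

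| Boundary | Interim p | Final p | Overall error |
|---|---|---|---|
| O'Brien-Fleming-type spending (Lan-DeMets) | 0.0031 | 0.0490 | 5.0% |
| Haybittle-Peto | 0.001 | 0.05 | 5.02% |
| Classical O'Brien-Fleming | 0.0052 | 0.0480 | 5.0% |

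For the spending function, the interim limit comes from 2·[1 − Φ(2.241/√0.5)] = 0.00153 per side, or 0.00305 two-sided.

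**Power cost.** At 87 per arm, final test at 0.0490 instead of 0.05, two-sided: 75.3% against 75.6%, a loss of 0.3 points.

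**The case against.** The strongest reply is that the article never says p<0.05 applies at the interim, that success may be declared there, or that the trial would stop. A reader might infer all three from the heading and the single threshold, but the text does not state them. If the interim can never lead to stopping or a claim, there is no inflation. The article also condenses a fuller protocol that is not shown and may contain a boundary. This stands as a limit on the claim, which must be conditional. It does not remove the point: the article itself commits to an efficacy look, gives one unrestricted threshold and sizes the trial on one test, and those statements taken together produce two unadjusted tests.

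Blinding the investigators does not answer it. Blinding limits operational bias, whereas the error rate depends on how often the arms are compared.

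A second reply is that 8% ignores the Yates correction named in the plan. That is right as far as it goes: with Yates the two-look error is about 6.0%, roughly one point above 5%. The relative rise is nevertheless similar.

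A third is that no figure in the article shows how many transfusions occur after discharge, or how many patients would be incomplete at half recruitment. The harm from the recruitment trigger is therefore unquantified. The mismatch between trigger and endpoint window remains.

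Two further readings should be resisted. The comparison of three arms raises its own multiplicity question, which is separate and should not be added to the cost of the interim look. And a reader might take the imbalance check as a set of significance tests; the section says only that imbalances are to be detected, and names no test. Calling age, sex and similar factors secondary endpoints is a slip of wording.

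**Conclusion.** The point holds in conditional form. The section announces stopping rules and plans an efficacy look, but states neither a boundary nor a consequence, and the only threshold available is p<0.05. If that threshold is used at both looks and success can be declared at either, the type I error for EPOFE vs placebo goes from 5% to about 8% (8.3% two-sided, 8.0% one-sided), or from about 3.8% to 6.0% with Yates.

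These figures assume one contrast and an information fraction near 0.5; the Yates figures also assume a common transfusion rate of 60%. Incomplete 60-day follow-up could push the interim information fraction below 0.5, which raises the unadjusted figure slightly. The article does not support the firmer statement that the trial will be stopped on p<0.05 at half recruitment. The recruitment trigger does not match the primary endpoint's 60-day window, but the size of that effect cannot be derived from the article.

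**What to change.** Before the interim takes place, amend the section in one of two ways.

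1. State a boundary for EPOFE vs placebo that holds the overall two-sided error at 5%, and say what follows if it is crossed. Examples are O'Brien-Fleming-type spending with p<0.0031 at the interim and p<0.0490 at the end, or Haybittle-Peto with p<0.001 and then p<0.05. Which one is a matter of preference. These limits are two-sided; if the sponsor intends the one-sided test used for the sample size, they must be recomputed on that basis. If the information fraction at the look differs from 0.5, the spending function gives the adjusted limits.
2. Alternatively, state that the interim cannot lead to stopping for efficacy or to an efficacy claim. Then no adjustment is needed.

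In either case, trigger the look when half of the patients (153 of 306) have completed the 60-day window after discharge, instead of when they have been recruited.

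The cost is one paragraph, about 0.3 points of power under the O'Brien-Fleming-type option, and a slightly later interim.
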